### Assignment of intervention/control groups

The assignment will be randomized by clusters (PCC).

Once the centres have been recruited, they will be stratified and matched according to the following variables: teaching/nonteaching status, classification according to the MEDEA index, percentage of assigned population of migrant origin and number of family doctors and primary care nurses with assigned quotas.

Centres with similar characteristics will be randomly assigned to the control or intervention group. The allocation of PCCs to each group will be made by a person outside the circle of researchers using a table of random numbers.

The individuals in the control group will be able to carry out the training activity once the study will be completed.

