## Statistical analysis

### Calculation of sample size

The sample size was determined based on findings from a pilot test involving pre- and post-intervention assessments conducted on 35 health professionals. Using the mean intervention effect (the mean test score improvement) and its standard deviation to estimate the expected intervention effect and within-group variability in the pilot test, the mean improvement was 2.07, with a standard deviation of 4.07. Assuming an alpha error of 0.05, a beta error of 0.2, and a design effect factor of 2 and expecting a 20% loss to follow-up after a 6-month period, the required sample size would be 262 (131 per group).In addition, the proportion of the LGTBIQ + population was considered to carry out a subsequent analysis from a gender and LGTBIQ + perspective. To estimate the proportion of LGTBIQ + professionals, data from the IPSOS (DeSilets et al. (DeSilets et al. [22])) survey were used; 14% of the Spanish population is estimated to belong to this group. This is the same proportion obtained in the sample of the pilot test (5 individuals (14.29% of the 35 participants) identified as LGTBIQ + ..

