### Planned analysis

For the treatment and analysis of the data, a descriptive analysis of the variables (percentages and averages with measures of dispersion) will be carried out according to the nature of the variables.Demographic and background data: descriptive statistics will be used (mean, median, standard deviation, range) to summarize the characteristics of the participants, including age, sex, years worked, etc. The distribution of test scores will be used to observe the distribution of pre- and postintervention test scores.Sensitivity analysis of the instrument: Analyses will be repeated using different methods to verify the robustness of the results.Comparison of baselines – Mann‒Whitney U or independent sample T-tests: whether the groups will be comparable in terms of demographic characteristics and baseline scores. Chi-square tests will be used to compare categorical proportions between groups (if applicable).Analysis of the effect of the intervention: T-tests for dependent samples or Wilcoxon signed-rank tests will be used to compare pre- and postintervention values within the same group. ANCOVA (analysis of covariance): to control for confounding or baseline variables, ANCOVA could be useful. Mixed analysis of variance (ANOVA): for multiple repeated measures (for example, pre, post- and 3-month follow-up).Cluster analysis (if applicable): Multilevel analysis or mixed models. These models will be useful for considering the hierarchical nature of clusters in the data.Lost data management – sensitivity analysis: To determine if missing data affects the results. Imputation techniques such as multiple imputation could be used if there is a significant amount of missing data.

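### Centres are randomised and a design effect of 2 is assumed, yet the only analysis that accounts for centre is conditional; without it, a between-arm ANCOVA or mixed ANOVA would have a type I error of about 16.6%

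*Protocol article*

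**What the plan says.** **Design.** Under Assignment of intervention/control groups, the unit of randomisation is the primary care centre, without qualification. Recruited centres are grouped first: "they will be stratified and matched according to the following variables", namely teaching status, MEDEA class, percentage of migrant population and staff numbers. Then "Centres with similar characteristics will be randomly assigned to the control or intervention group".

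**Sample size.** Calculation of sample size takes its effect and variability from a pilot in which "the mean improvement was 2.07, with a standard deviation of 4.07". It continues: "Assuming an alpha error of 0.05, a beta error of 0.2, and a design effect factor of 2", with 20% loss, giving 131 per group. The design effect is thus applied to a change score.

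**Analysis.** Planned analysis contains:
- Mann-Whitney or independent t-tests, and chi-square tests, to compare the groups at baseline;
- for the intervention effect, paired t-tests or Wilcoxon signed-rank tests within a group, ANCOVA (described as possibly useful) and mixed ANOVA for the repeated scores;
- as a separate entry, "Cluster analysis (if applicable): Multilevel analysis or mixed models", described as useful for the hierarchical structure.

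None of the methods listed for the intervention effect carries a centre, pair or stratum term. The section on possible confounders and effect modifiers does list the centre itself and the four matching variables.

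**The concern.** The design and the sample size treat clustering as certain; the analysis treats it as something that may or may not apply. In a trial that allocates whole centres it always applies, because professionals in one centre share colleagues, patients, training and allocation.

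The word mixed in mixed ANOVA does not help. As described, that method handles repeated scores from one person, not the correlation between people in the same centre.

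The between-arm comparison is at stake. The Discussion expects better results in the intervention groups than in their control groups. If that comparison is made with professionals treated as independent, the standard error is too small, the interval too narrow and the false-positive rate too high. The choice is not deferred to another document: the article lists the methods and attaches the condition itself.

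**Working it through.** **Inputs.** Design effect (DE) 2, alpha 0.05, beta 0.2, difference 2.07, SD 4.07, loss 20% and 131 per group, all from Calculation of sample size. Sidedness is not stated; two-sided is assumed. No intracluster correlation (ICC), cluster size or final number of centres is given.

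**1. The plan's own figure.** n per arm = 2 × [4.07 × (1.960 + 0.842) / 2.07]² = 60.7, rounded up to 61. Times DE 2 = 122. Divided by 0.80 = 152.5, so 153 per arm. The stated 131 does not reproduce; one-sided, paired and other loss-inflation variants do not give it either. That is a separate matter. The type I error below depends on the design effect, not on N. The DE that 131 would support is 131 × 0.8 / 60.7 = 1.73, close to the 1.75 row in step 3.

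**2. Error when clustering is ignored.** If the true variance of the between-arm difference is DE times the variance the analysis assumes, the test statistic has standard deviation √DE under the null:

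type I error = 2 × [1 − Φ(1.96 / √DE)]

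At DE = 2: 1.96 / 1.414 = 1.386, and 2 × [1 − Φ(1.386)] = 0.166. The interval has 1/√2 = 0.71 of its proper width, about 29% too narrow.

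**3. Range over the design effect.**

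| DE | Type I error | Interval too narrow by (1 − 1/√DE) |
|---|---|---|
| 1.25 | 8.0% | 11% |
| 1.5 | 11.0% | 18% |
| 1.75 | 13.8% | 24% |
| 2 | 16.6% | 29% |
| 3 | 25.8% | 42% |

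**4. Check by simulation.** Each scenario had 20,000 trials with 7, 10 or 13 centres per arm and 15, 10 or 8 professionals per centre. The ICC was set to 1/(m − 1), with m the professionals per centre (0.071, 0.111, 0.143), so that DE = 2. These layouts are assumptions. The individual-level test was a two-sample t-test, standing in for an ANCOVA or mixed ANOVA without a centre term.

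| Share of between-centre variance explained by matching | Individual-level test | Unpaired test on centre means | Paired test on centre means |
|---|---|---|---|
| None | 16.7–16.9% | 5.0–5.1% | 5.1% |
| Half (assumed) | 9.8–10.6% | 2.1–2.6% | 4.8–5.1% |

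Ignoring the centre inflates the error in both rows. Ignoring effective matching in a centre-level test makes that test conservative. A test that respects both centre and matching holds about 5%.

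**The case against.** The strongest reply is that the plan does not ignore clustering: it names multilevel or mixed models and says what they are for. That stands, and it limits the point. The 16.6% arises only if that option is not taken. The defect is an uncommitted choice whose stated condition conflicts with the design.

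A condensed article may also leave degrees of freedom and pair or stratum terms to a fuller document. That stands too. Their absence is no finding in itself; they appear below only as part of a sound replacement.

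Four stronger readings are tempting, but the document does not support them.

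- **That the planned t-tests of the effect run at about 17%.** Those t-tests are paired and within one group. Clustering distorts their standard errors, but they do not compare arms. The independent-sample tests are named for baseline only. The inflated between-arm error concerns ANCOVA and mixed ANOVA.
- **That the unused matching causes the inflation.** It does not. Matching that works lowers the error of the individual-level test (to about 10% in the half-variance scenario), and ignoring it at centre level gives a conservative test.
- **That the matching is never used.** No pair or stratum term is named, but the matching variables and the centre are listed as possible confounders or effect modifiers, and ANCOVA is meant to control for confounding.
- **That the plan relies on large-sample z-tests with 13 centres.** No such test is mentioned. The 13 centres marked in Table 2 are those already enrolled out of 46 invited, an interim count.

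**Conclusion.** The point holds in conditional form. Centres are randomised and a design effect of 2 is assumed, so making the centre-accounting analysis conditional contradicts the trial's own design. If that option is skipped, a between-arm ANCOVA or mixed ANOVA at nominal 5% would have a type I error of about 16.6%, more than three times nominal, with 95% intervals about 29% too narrow.

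This rests on a two-sided test, on the protocol's design effect holding for the score analysed, and on matching that explains none of the between-centre variance. With other design effects the error runs from about 8% (1.25) to about 26% (3). It falls below 16.6% if the matching is effective, yet was still about twice nominal when matching explained half of the between-centre variance. Every case examined exceeds 5%. The text needs correcting before analysis, because the between-arm comparison carries the effectiveness claim.

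**What to change.** In Planned analysis:

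1. Delete the parenthesis that makes the cluster analysis conditional.
2. State that the main between-arm analysis, for knowledge scores and for clinical outcomes, is a mixed model with a random effect for centre, of a type suited to the outcome and adjusted for baseline where a baseline value is available. An analysis of centre-level summaries is an acceptable alternative.
3. Reflect the allocation in that model, through the matched sets or the matching variables. With few centres, pair terms use scarce degrees of freedom, so choose between the two before outcome data are seen.
4. Name a small-sample correction to be used if few centres enrol, for example Kenward-Roger or Satterthwaite degrees of freedom, or a t reference for centre-level summaries.
5. Label the within-group paired tests and the baseline tests as descriptive, and state that they do not support the effectiveness claim. ANCOVA or mixed ANOVA without a centre term should not be used for inference between arms.

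**Cost.** A change of wording in one section. P-values and intervals will be less favourable than those from an analysis that ignores centre. No new data are needed.

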### Limitations

The intervention to be assessed cannot be masked since it could influence its effect. Because there is a possibility of contamination bias among professionals, randomization by clusters is proposed under the assumption that the number of clusters would be sufficient for each group.

Geographic dispersion of the PCC will reduce the possibility of contamination.

Participants will know they are being assessed, which could lead to observer bias, although comparisons with a control group who will also know they are being observed may reduce the effect of this bias in the surveys. On the other hand, regarding the clinical variables of the professionals, it is thought that the observation time is long enough that the fact that they are being observed does not interfere with their clinical use.

## Discussion

We expect to obtain a validated educational tool that, through gamification, allows primary care professionals to increase their knowledge of sexuality, sexually transmitted infections, and the prevention and detection of violence, improving the results of the evaluation test after the educational intervention.

Expected results:An increase in the knowledge of sexuality, sexually transmitted infections, and the prevention and detection of violence among primary care professionals, as well as an improvement in the results of the evaluation test after the educational intervention and improved results in the participants of the intervention groups compared to their control groups.An increase in the number of diagnostic and screening tests performed after the intervention in comparison to the control group.A better recording of diagnoses and more appropriate antibiotic treatments for the groups of professionals for whom the intervention will be carried out.

The aim of this study is to evaluate the tool used by primary care professionals But in the near future it is expected to be possible to play the game at different levels of difficulty.. The level of difficulty will depend on the videogame players: professionals, university students of health sciences or patient populations as young people.

We expect to build an educational tool that motivates active participation and facilitates acquisition of knowledge and safe behaviours related to sexual health in the short and medium term, including the prevention and detection of violence based on gender, sexual identity or orientation, access to the health system, and prevention, detection, and treatment of sexually transmitted infections. Likewise, we expect this tool to be a facilitator of health education for at-risk or vulnerable groups.

## Data Availability

The datasets used and/or analysed during the current study are will be available from the corresponding author on reasonable request.

## Abbreviations

LGTBIQ +: Lesbian, gay, bisexual, trans, intersex, queer and plus
PC: Primary care
PCC: Primary care centre
PCR: Polymerase chain reaction
RCT: Randomized controlled trial
STI: Sexually transmitted infections
